## Abstract

**Background:**

This protocol describes a study that will test the effectiveness of a 10-week non-clinical psychological coaching intervention for intentional personality change using a smartphone application. The goal of the intervention is to coach individuals who are willing and motivated to change some aspects of their personality, i.e., the Big Five personality traits. The intervention is based on empirically derived general change mechanisms from psychotherapy process-outcome research. It uses the smartphone application PEACH (PErsonality coACH) to allow for a scalable assessment and tailored interventions in the everyday life of participants. A conversational agent will be used as a digital coach to support participants to achieve their personality change goals. The goal of the study is to examine the effectiveness of the intervention at post-test assessment and three-month follow-up.

**Methods/Design:**

A 2x2 factorial between-subject randomized, wait-list controlled trial with intensive longitudinal methods will be conducted to examine the effectiveness of the intervention. Participants will be randomized to one of four conditions. One experimental condition includes a conversational agent with high self-awareness to deliver the coaching program. The other experimental condition includes a conversational agent with low self-awareness. Two wait-list conditions refer to the same two experimental conditions, albeit with four weeks without intervention at the beginning of the study. The 10-week intervention includes different types of micro-interventions: (a) individualized implementation intentions, (b) psychoeducation, (c) behavioral activation tasks, (d) self-reflection, (e) resource activation, and (f) individualized progress feedback. Study participants will be at least 900 German-speaking adults (18 years and older) who install the PEACH application on their smartphones, give their informed consent, pass the screening assessment, take part in the pre-test assessment and are motivated to change or modify some aspects of their personality.

**Discussion:**

This is the first study testing the effectiveness of a smartphone- and conversational agent-based coaching intervention for intended personality change. Given that this novel intervention approach proves effective, it could be implemented in various non-clinical settings and could reach large numbers of people due to its low-threshold character and technical scalability.

## Background

There is a recent debate in personality science whether and how personality traits can be intentionally modified or changed over short periods of time by intervention efforts. Although available research suggests that most people want to change or modify some aspects of their personality [1–3], psychological interventions for intentional personality change are almost lacking. Only a few studies have examined intentional personality change over shorter periods of time [4–6]. These very few existing studies are promising and suggest that intended trait change in a desired direction is possible. However, it is still an open question whether personality change can be maintained or rather reflects temporary changes that revert over time. This protocol describes a study that will test the effectiveness of a non-clinical psychological coaching intervention for intentional personality change that focuses on the Big Five personality traits, i.e., neuroticism, extraversion, openness to experience, agreeableness, and conscientiousness.

## Conceptual Framework of the Intervention

Since intervention efforts for intended personality change are in their infancy, conceptual frameworks are needed to develop theory-driven intervention programs. One approach would be to carefully develop specified treatments/treatment guidelines for changing particular personality traits. The other approach would be to develop interventions based on more general (common) intervention principles [7]. The present coaching intervention is based on a general (common) change mechanisms intervention framework. General change mechanisms are assumed to be responsible for intermediate changes in someone’s characteristics, skills, experiences, and behaviors, and eventually lead to improvements in the ultimate outcome or targeted goal of an intervention. Allemand and Flückiger [7] argue that four empirically derived general change mechanisms from psychotherapy process-outcome research [8–11] provide useful heuristic principles for intentional personality change interventions and help to maximize the effectiveness of intervention efforts. The four mechanisms are: (1) actuating discrepancy awareness, (2) targeting thoughts and feelings (insight), (3) targeting behaviors (practice), and (4) activating strengths and resources. These mechanisms highlight different perspectives of the immediate individual psychological outcomes and are highly connected with each other [12]. In order to target those general change mechanisms and to promote the change process, the coaching intervention includes several micro-interventions. Micro-interventions (specific tools and techniques) are small interventions that are essential in helping individuals to modify or change trait-related experiences and behaviors in concrete real-life situations and help to maintain the change process [13].

### Actuating discrepancy awareness

The first change mechanism focuses on the awareness of differences between the actual and the desired personality, which might facilitate the change process. The idea is that personality traits can be most effectively targeted and altered while people explore potential gaps between their actual and desired personality (cf. [14]). Examples of micro-interventions that target this change mechanism are (a) the motivational interviewing approach, (b) miracle questions, and (c) individualized progress feedback. The *motivational interviewing approach* [15] serves to counterbalance advantages and disadvantages of change and might eventually enhance individual change motivation. By writing down pros and cons of the actual and desired behavior and experience, people can evaluate the gap between their actual and desired personality. *Miracle questions* help people to think about their future goals and their desired personality and thus actuate discrepancy awareness between the actual and the desired personality. Miracle questions are basically thought experiments, which ask people to imagine their desired future and personality [16]. Individually tailored *progress feedback* is one of the most commonly used change techniques in smartphone-based health interventions [13] that helps people to focus on their discrepancy awareness.

### Targeting thoughts and feelings to realize insight

The second mechanism emphasizes reflective processes, which may promote the personality change process by helping individuals to reflect their thoughts, feelings, and behaviors in a more systematic way. The following five micro-interventions are known to be effective to activate this change mechanism: (a) systematic reflection, (b) psychoeducation, (c) observational learning, (d) introspection, and (e) identification of situational/contextual triggers. *Systematic reflection* is a micro-intervention that helps people to learn from experiences including failures and successes [17]. Changing aspects of one’s personality is hard and is related to experiences of failures. Systematic reflection helps to focus on the goal rather than on emotional reactions after a failed task. To promote the change process, it is also important to understand own beliefs and expectations. Since people may have different self-theories about the changeability of different aspects of personality [18], fostering the knowledge transfer about personality change in the form of *psychoeducation* may further promote the change process. Psychoeducation is a prominent tool in cognitive behavioral therapy [19]. Other micro-interventions, which also target thoughts and feelings, are the observation and modeling of others’ behaviors (*observational learning*) [20, 21], watching one’s own behaviors, thoughts, and feelings (*introspection*) [21, 22], and identifying *situational and contextual triggers* (e.g., people, society, surroundings; [23]). Being aware of situational and contextual triggers, which are connected to the desired or actual behavior, can actually help to show desired behaviors more often and to avoid actual behaviors [23].

### Targeting behaviors to realize practice

This mechanism focuses on learning and reinforcing new behaviors and skills, such as compensatory or coping skills, and to behave in new roles. To achieve change goals, individuals should gradually increase engagement in activities and new behaviors connected to their change goals. Two micro-interventions are included in the intervention to target this change mechanism: (a) implementation intentions and (b) behavioral activation. Generating *implementation intentions* in the form of specific “if-then plans” can lead to better goal attainment and help individuals in habit formation [24]. This micro-intervention was successfully used in previous intervention work for intentional personality change [5]. *Behavioral activation tasks* help individuals to perform novel behaviors and activities. Behavioral activation is based on principles of reinforcement and learning theory and was originally developed for the treatment of depression [25]. Magidson and colleagues’ [26] suggest this micro-intervention also for intentional personality interventions and used it in their case study.

### Activate strengths and resources to realize strengths-orientation

This change mechanism capitalizes on individual and interpersonal strengths and resources. Resources might be related to personal skills and capabilities, motivational readiness and preparedness for change, as well as social support. Micro-interventions identified to target this mechanism include (a) organizing a change team, (b) keeping a diary of strengths and resources, (c) using the tree of resources, and (d) thinking about future plans, dreams and hopes. An informed *change team*, including significant others such as friends and family members can provide social support throughout an intervention and help people to attain their change goals [27]. Keeping a *diary of strengths and resources* [28] or to write down individual resources inside the *tree of resources* [8, 29] can further promote the change process by reflecting about personal strengths and positive aspects of life. Another micro-intervention activates individuals’ resources and enhances change motivation by *thinking about future plans, dreams and hopes* by getting asked questions derived from the life story interview approach [30].

## Smartphone-Based Coaching Interventions

Smartphones provide a powerful tool set for psychological and behavioral micro-interventions for several reasons [31–38]. First, smartphones are ubiquitous with increasingly powerful technical abilities and make sophisticated micro-interventions appealing and widely applicable. Second, unlike desktop computers, laptops or tablets, smartphones are nearly always with the person. Third, people often have a positive emotional attachment to and daily routines in dealing with their smartphones, which can reduce the barriers to adoption and increase acceptance of micro-interventions. Fourth, the combination of powerful technical abilities of smartphones and their proximity to their owners offers the ability to detect useful context information that can be used to individualize interventions. Moreover, context awareness features enabled through sensing and phone-based personal information allows creating just-in-time micro-interventions that provide users with support at times when that support is most needed. Finally, interventions using smartphones are scalable, cost-effective, low-threshold, applicable to a wide variety of participants and show promising retention rates. For example, a recent study in the public health context found that owning a smartphone “was not a major barrier to study participation for most respondents [...] including those who were unemployed”, i.e. with a low socio economic status [39]. In another recent study, retention rates of smartphone-based interventions are promising as participants had eight conversational turns with a smartphone-based chatbot per day on average over the course of six months [40, 41].

### The talk-and-tools-paradigm

Smartphone interfaces also enable the application of the so-called talk-and-tools paradigm [42, 43]. That is, smartphones are able to offer scalable communication features with the help of conversational agents (the *“Talk”*, e.g., for motivational interviewing purposes), i.e., computer programs that imitate a conversation with a human being [44–47]. In contrast to popular voice-based conversational agents such as Amazon’s Alexa, Apple’s Siri, text-based conversational agents (often called “chatbots”) are so far less prominent. Promising examples include Florence (getflorence.co.uk), Lark (web.lark.com) or Woebot (woebot.io). In contrast, interfaces of smartphones can also be used to deliver a broad range of *“Tools”*, i.e., the building blocks of micro-interventions (e.g., keeping a diary of resources, a reminder for individual implementation intentions or the delivery of psychoeducation video clips). The application of this talk-and-tools paradigm can not only complement and extend existing face-to-face counseling sessions to the everyday life of individuals, but it can also provide new means to offer smartphone-based coaching interventions in a scalable fashion where a personal coaching approach is not feasible due to limited reach, personnel or budget.

### Design of conversational agents

Due to limited evidence on effective designs of text-based conversational agents on mobile devices [48, 49], it is essential to study design features of conversational agents and how they help individuals to reach their goals. Conversational agents are designed to interact with a human – like a human. The *Computers as Social Actors* theorem by Reeves and Nass [50] confirms that individuals apply social behaviors and heuristics typical for social interactions with other human beings to interactions with computers – and conversational agents.

Research in the field of counselling psychology and psychotherapy has shown that *working alliance,* a collaborative quality and the degree to which health professionals and patients engage with each other, is associated with the therapeutic process and robustly linked to treatment success in face-to-face therapy as well as in online therapy (*r* = .28; [51]) [52, 53]. The concept of working alliance can be adapted to the “relationship” between individuals and conversational agents and their interactions (e.g., quality and length of messages exchanged or frequency of interactions). It can be expected, that when a conversational agent takes over the role of a communication partner and embodies a digital coach, its communication style and role will affect relationship-building processes and, in part, treatment success (e.g., [54, 55]).

Hence, it can be assumed that the choice of specific verbal cues will increase an individual’s working alliance with a conversational agent. The present conversational agent-based intervention will focus on one specific verbal cue, namely whether the chatbot can refer to itself using the first-person pronoun “I”. The use of “I” automatically implies a sense of human self-awareness or self-concept by the chatbot [56], making it more anthropomorphic and relatable, than a conversational agent without a self-concept.

In order to test the effects of a self-aware versus a non-self-aware conversational agent on working alliance and intervention effectiveness, two conversational agents will be experimentally manipulated, such that a “self-aware” conversational agent will present itself as a tangible and present entity by actively referring to itself (“May I help you?”) in contrast to an impersonal control conversational agent which will refrain from referring to itself (“Do you need help?”) and remains less tangible as an entity, fading the anthropomorphic identity of the conversational agent into the background. The overall conversational streams, message lengths, coaching elements, and schedule will be kept the same in both conditions.

## Research Goals and Hypotheses

The first goal of the present study is to examine the effectiveness of PEACH, a smartphone- and conversational agent-based coaching intervention for intentional personality change. The outcome research hypothesis is that two experimental conditions (high versus low self-aware conversational agent) will be more effective with respect to personality trait change in comparison to the two waiting list conditions. Furthermore, based on previous work on the effects of anthropomorphized computer-mediated communication on human behavior [57], the differential outcome research hypothesis is that the self-aware conversational agent will be more effective in terms of relationship-building, promoting intervention adherence and thus treatment success than the low self-aware conversational agent.

The second goal is to explore underlying processes and mechanisms that improve the outcomes of the intervention. Two approaches are used for process assessments: self-reports and smartphone sensing. Both methods include an intensive longitudinal design. This allows exploring associations between actively (self-reports) and passively (sensors) assessed intervention processes.

## Methods/Design

### Design

In this study protocol, we describe a 2x2 factorial between-subject randomized, wait-list controlled trial with intensive longitudinal methods studying the effectiveness of a 10-week smartphone- and conversational agent-based coaching intervention for intentional personality change. The effectiveness of the intervention will be compared across two dimensions: intervention (experimental versus wait-list control) and conversational agent design (high versus low self-awareness). Participants will be randomly assigned to one of four conditions: (a) experimental condition 1: conversational agent with high self-awareness, (b) experimental condition 2: conversational agent with low self-awareness, (c) wait-list condition 1: conversational agent with high self-awareness, (d) wait-list condition 2: conversational agent with low self-awareness. Participants in the wait-list control conditions will receive no intervention for the first four weeks to document the natural course of their personality change without expecting interventional effects. To monitor progress, the wait-list control groups will respond to the same weekly questionnaires during those four weeks as the subjects from the experimental conditions. Additionally, they are passively tracked by smartphone sensors. After the four weeks without any intervention, subjects of the wait-list control conditions will receive the same intervention as subjects of the experimental conditions - depending on their conversational agent embedding high or low self-awareness cues.

### Participants and Recruitment

The targeted sample will include at least 900 German-speaking adults, who install the PEACH App on their smartphones, give informed consent, pass the screening, fill in the pre-test assessment and start with the intervention. To assure an adequate power to detect statistical significance and to demonstrate a small to medium effect of a pre-post time by group interaction we require data from 300 participants. Assuming an α error level of 0.05, a statistical power (1-β) of 0.80, and a correlation of 0.40 between the pre- and post-measurements and 75 completers for each group, we would be able to detect a small effect of Cohen’s *d* = .22. Computing power for repeated measures, which is the case in this study, is more complex. As such, this power analysis only gives a rough idea of the effect sizes the study could reasonably detect. In a similar study [33], 67% of participants completed the post-test survey after 6 weeks, from a cohort of 273 who started the intervention. Based on this estimate and taking the longer duration of this study into account, we expect even more attrition. Should drop-out rates be higher than expected, we may recruit additional participants to ensure sufficient statistical power. To be eligible for the study, participants must be: (1) 18 years or older; (2) able to read German; (3) not in a psychotherapeutic or psychiatric treatment; (4) owner of a smartphone (Android or iOS) with mobile internet connection; and (5) interested and motivated to participate at the intervention and to change some aspects of their personality. The focus of this intervention study is explicitly on healthy adults. Thus, adults with mental health disorders and other psychosocial problems will be excluded. Participants will complete an online eligibility screening that checks for the inclusion criteria. Excluded candidates with mental health disorders and psychosocial problems will be provided with an information and contact details of the psychological counseling service of the University of Zurich.

We will primarily use university mailings and social media advertisements for the recruitment process. Additionally, potential participants will respond to flyers or word-of-mouth recruitment. Interested people will be directed to either the website of the project (www.personalitycoach.ch) or to the Apple Store/Google Play Store to receive detailed information about the study aims, interventions, assessments, reimbursement, and data protection and download the mobile application. Participants will be automatically and randomly assigned to one of four conditions (Fig. 1). In total, the two experimental conditions will be oversampled and will include 2/3 and the control condition 1/3 of all participants (full randomization in all four conditions). The automated allocation and randomization procedures will be computer generated. In this way, we aim to ensure that the conditions are fully randomized with respect to the participants’ baseline characteristics (allocation concealment). Because all participants will be treated using a comparable coaching intervention, participants are blinded to the two conversational agents. Spill-over effects could occur since participants might know each other and talk about the procedure of the intervention. After obtaining informed consent and passing the screening assessment, participants will be directed to the pre-test assessment. The procedure and design of the study are also depicted in Fig. 1.

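### The power statement assumes four equal groups of 75, but the 2/3 : 1/3 allocation turns 300 completers into about 100/100/50/50

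*Protocol article*

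**What the plan says.** All the figures are in the protocol article under Participants and Recruitment. The recruitment target is at least 900 adults who start the intervention. For power, the article says "we require data from 300 participants". Its inputs are "Assuming an α error level of 0.05", "a statistical power (1-β) of 0.80", "a correlation of 0.40 between the pre- and post-measurements" and "75 completers for each group". With these, "we would be able to detect a small effect of Cohen’s *d* = .22". The effect in question is a pre-post time by group interaction.

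On attrition, the article cites a similar study in which "67% of participants completed the post-test survey after 6 weeks". It expects heavier loss here without giving a rate, and it allows further recruitment if drop-out exceeds expectation. It describes the power analysis as approximate.

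On allocation, the next paragraph of the section says that "the two experimental conditions will be oversampled and will include 2/3 and the control condition 1/3 of all participants". The Design section sets out four conditions: two experimental and two wait-list.

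**The concern.** Four conditions at 75 each make 300, so the power statement treats the groups as equal in size. The allocation paragraph makes them unequal by design. A total of 300 completers then cannot supply 75 in every group.

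The contrast affected is the one behind the first hypothesis, the two experimental conditions against the two wait-list conditions. For a fixed total, a 2:1 split is less precise than 1:1, so the published figure describes a slightly better design than the one to be run.

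**Working it through.** **Inputs from the article:** alpha 0.05 (sidedness not stated; two-sided assumed), power 0.80, pre-post correlation 0.40, 75 per group, total 300, 900 starters, allocation 2/3 : 1/3.

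**Assumptions made here:** equal split within each pair of conditions (2:2:1:1) and equal retention in all arms.

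**1. The plan's own figures.** 4 × 75 = 300, so the count reproduces with equal groups. For d, take the F test of a repeated-measures group-by-time interaction with two time points, noncentrality λ = f² × N × 2 / (1 − 0.40) and d = 2f. Four equal groups and N = 300 give f = 0.105, so d = 0.21. Rounding f to 0.11 before doubling gives .22. This is the closest match at N = 300 among the variants tried; two equal groups, for example, give 0.178. The gap between 0.21 and .22 is small and on the cautious side, and it does not bear on the allocation.

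**2. Group sizes under the stated allocation.**
- 300 completers: 300 × 2/3 ÷ 2 = 100 per experimental arm; 300 × 1/3 ÷ 2 = 50 per wait-list arm.
- 900 starters: 300/300/150/150.
- 75 per wait-list arm: 75 × 2 ÷ (1/3) = 450 completers, and 450/900 = 50% retention.

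| Common retention | Total completers | Per experimental arm | Per wait-list arm |
|---|---|---|---|
| 33% (300/900) | 300 | 100 | 50 |
| 40% | 360 | 120 | 60 |
| 50% | 450 | 150 | 75 |
| 60% | 540 | 180 | 90 |
| 67% | 603 | 201 | about 100 |

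**3. Precision of the pooled contrast at 300 completers.** The standard deviation of a change score, in baseline SD units, is √(2 × (1 − 0.40)) = 1.095. The detectable difference is (1.96 + 0.84) × 1.095 × √(1/n₁ + 1/n₂).
- 150 v 150: √(1/150 + 1/150) = 0.1155, giving 0.354.
- 200 v 100: √(1/200 + 1/100) = 0.1225, giving 0.376.
- Ratio: 0.1225 / 0.1155 = 1.061.
- Power at 0.354 with 200 v 100: 0.354 / (1.095 × 0.1225) − 1.96 = 0.68, which corresponds to 0.75.

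The change-score figures are on a different scale from the article's d and do not replace it. Scaling the article's figure by the same ratio gives .22 × 1.061 = about .233.

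**4. Total that restores 150 v 150.** At 2:1, 1/n₁ + 1/n₂ = 4.5/N. Setting 4.5/N = 2/150 gives N = 337.5, so about 338 completers (37.5% of 900).

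**5. Agent comparison.** Pooled over all arms it is 100 + 50 = 150 against 100 + 50 = 150, the same as with equal groups.

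**The case against.** **The 900 target.** A reader might infer that the wait-list arms cannot reach 75 completers. The article does not support that. With 900 starters each wait-list arm begins with about 150 and has 75 completers at 50% retention, and extra recruitment is allowed. The only retention figure cited is 67% at 6 weeks. This objection stands. A shortfall against 75 arises only below 50% retention, which is possible because the article expects heavier loss than in the cited study, but is not certain.

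**Later wait-list post-test.** A reader might also infer that wait-list retention will be lower, since that post-test comes four weeks later. That is an inference, not a stated fact. Suppose the cited 67% is extended as a constant weekly hazard (an assumption), with post-test at 10 to 12 weeks in the experimental and 14 to 16 weeks in the wait-list conditions. Completers are then about 269 to 308 experimental and 103 to 118 wait-list. The formula above gives 0.356 (269 v 103) to 0.332 (308 v 118), about equal to or better than the 0.354 benchmark. In addition, the Design section confines the untreated wait-list period to the first four weeks, so post-test retention does not govern every comparison with control.

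**Comparisons and checks the plan does not state.** The article states neither a comparison of the two agents within the wait-list alone nor a recruitment check at 300 completers. Its trigger for more recruitment is drop-out above expectation.

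**Approximate by its own account.** The article calls the power analysis rough. That caveat is attached to the complexity of repeated measures. It makes the point less important but does not reconcile the group sizes.

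**Conclusion.** The inconsistency is in the text. Under the stated allocation, a total of 300 completers and 75 in each group cannot both hold, and the published detectable effect rests on group sizes that the design does not give. If completers total exactly 300, the loss is about 6% in standard error for the pooled intervention contrast, or about five percentage points of power. With 338 or more completers at 2:1, that contrast is at least as precise as the 150 v 150 case. The result rests on equal splits within pairs, equal retention and a two-sided test on change scores. It does not show that the trial is underpowered or that the wait-list arms will fall short. Severity: minor.

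**What to change.** Recompute the power statement under 2:2:1:1 allocation, and give one of the following together with an explicit retention assumption:
- the detectable effect at 100/100/50/50 completers; or
- the total completers needed: about 338 for the pooled precision of 150 v 150, or 450 if 75 per wait-list arm is intended.

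The split within each pair of conditions should be stated too. The cost is a corrected sentence or two and, if the total stays at 300, a slightly less favourable figure. Allocation and the target of 900 starters can stay as they are.

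### The detectable effect of d = .22 for 300 completers does not match its stated inputs: for experimental versus wait-list they give about 0.35 to 0.38 on pre-post change, or about 0.30 to 0.31 with pre-test adjustment

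*Protocol article*

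**What the plan says.** All the inputs stand in one paragraph of the protocol article, under Participants and Recruitment. The purpose is "to demonstrate a small to medium effect of a pre-post time by group interaction", for which "we require data from 300 participants". The settings are "Assuming an α error level of 0.05, a statistical power (1-β) of 0.80", with "a correlation of 0.40 between the pre- and post-measurements and 75 completers for each group". The result is that "we would be able to detect a small effect of Cohen’s *d* = .22". The article adds that repeated-measures power is more complex and that the calculation is only a rough guide. It does not state whether the test is one- or two-sided, which contrast is powered, or the SD unit of d.

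Two other places matter. Research Goals and Hypotheses states the main comparison as the two experimental conditions against the two waiting-list conditions. The paragraph on randomisation, also under Participants and Recruitment, puts two thirds of participants in the experimental conditions and one third in the control conditions. That does not match "75 completers for each group".

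**The concern.** A correlation of 0.40 is low for a change-score comparison. The SD of the change is then larger than the SD of a single measurement, so 150 versus 150 completers cannot plausibly resolve about a fifth of an SD with 80% power. The article prints every main input, so this is a check of its own arithmetic, not a request for detail that belongs in an analysis plan.

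At stake is what a reader takes the trial to be able to show. The figure accompanies the 300-completer requirement, and the article says it may recruit further to keep power sufficient. If sufficiency is judged against .22 at 300 completers, the yardstick is too lenient.

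**Working it through.** **Inputs.** α = 0.05, taken as two-sided because the article does not say; power 0.80; correlation ρ = 0.40; 300 completers. The experimental-versus-wait-list contrast has 150 versus 150 completers if each group has 75, or 200 versus 100 at 2:1. The multiplier is 1.960 + 0.842 = 2.802. The unit is the SD of a single measurement, assumed equal at pre- and post-test.

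**Attempt to reproduce .22.** For the interaction in a four-group, two-occasion repeated-measures ANOVA, λ = N·m·f²/(1 − ρ) = 300 × 2 × f²/0.60 = 1000 f². With 3 numerator df, 80% power needs λ = 11.05, so f = 0.105. Doubling gives 2f = 0.210. It becomes .22 only if f is first rounded up to .11, where power is 0.838 and the N required for 80% is 275. So even this nearest route does not return the printed figure exactly. Nor is 2f the difference in change: in a two-group, two-occasion interaction each cell deviates by a quarter of that difference, so the difference is 4f.

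**Change scores.** SD of change = √(2(1 − 0.40)) = 1.095.
- 150 versus 150: standard error = 1.095 × √(2/150) = 0.1265; detectable difference = 2.802 × 0.1265 = 0.354. Power at .22: 0.22/0.1265 = 1.739, and Φ(1.739 − 1.960) = 0.41.
- 200 versus 100: standard error = 1.095 × √(1/200 + 1/100) = 0.1342; detectable difference = 0.376. Power at .22: Φ(1.640 − 1.960) = 0.37.
- Cross-check by the F route with two groups: f = 0.0889, 4f = 0.356, in agreement with 0.354.

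**Pre-test-adjusted.** Residual SD = √(1 − 0.40²) = 0.917.
- 150 versus 150: 2.802 × 0.917 × √(2/150) = 0.296; power at .22 is 55%.
- 200 versus 100: 2.802 × 0.917 × √(1/200 + 1/100) = 0.314; power at .22 is 50%.

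**Other readings at 150 versus 150.**

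| Reading | Detectable d | Power at .22 |
|---|---|---|
| Change score, one-sided | 0.315 | 54% |
| d in units of the change SD, two-sided | 0.323 | 48% |
| Pre-test-adjusted, one-sided | 0.263 | 67% |

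None reaches .22. A two-sided change-score value of .22 would need ρ = 1 − (0.22/(2.802 × 0.1155))²/2 = 0.77. Two calculations land near .22 but discard a stated input: a one-sided paired test within one arm of 150 (0.223), which has no group comparison, and 600 versus 300 with no dropout from 900 (0.217).

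**The case against.** Four points can be made for the article.

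*The figure may be mislabelled, not miscalculated.* A four-group interaction f of about 0.105, doubled, comes close to .22, and the article does not define its d. This is plausible but unconfirmed. If it is right, the printed number is still not the standardised difference in change that a reader will take it to be.

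*The article calls the calculation rough, and plans more than a two-occasion comparison.* Data Analyses describes growth models, including models of the weekly self-reports, which the wait-list groups also complete during their four control weeks. Actual sensitivity may therefore differ from every figure above. That stands. But the printed statement concerns a pre-post interaction and already uses a pre-post correlation. Calling it rough does not cover a detectable effect understated by a factor of 1.6 to 1.7 on change scores (0.354/0.22, 0.376/0.22), or about 1.35 to 1.43 with adjustment.

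*More than 300 may complete.* At the cited 67%, 900 starters would give 603 completers, or 402 versus 201 at 2:1. The detectable difference would be 2.802 × 1.095 × √(1/402 + 1/201) = 0.27 on change scores and 0.22 with adjustment. But the article expects more attrition than that, and its claim is made for 300.

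*Equal completer numbers might arise from unequal dropout.* From 600 and 300 starters, 150 completers each would need 25% and 50% completion. The article assumes no such difference.

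A reader might also go further than the text allows. A detectable difference of 0.42, with 27% power at .22, follows only if the test is a 3-df comparison of all four groups. The article names no such test, and its hypothesis is a single contrast. It also does not show how 900 was derived from 300, so the recruitment target cannot be said to rest on .22. Nor does it plan to read a null result as excluding a small effect.

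**Conclusion.** The concern holds for the printed figure. With the article's inputs and its experimental-versus-wait-list hypothesis, 300 completers give 80% power for a difference in change of about 0.35 SD at equal numbers or about 0.38 at 2:1. At .22 the power is about 41% or 37%. Pre-test adjustment is the favourable bound, at about 0.30 to 0.31 and 50 to 55% power. These values assume a two-sided test, equal SDs at both occasions and d in single-measurement SD units; the one-sided and change-SD variants do not rescue .22.

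The conclusion is limited to that sentence and to the equal group sizes beside it. A value of about 0.35 still fits the article's aim of a small-to-medium effect, so the 300-completer requirement does not fall with the figure. The origin of .22 remains an inference.

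**What to change.** Correct the power statement and leave enrolment as it is.
- Name the contrast (pooled experimental versus pooled wait-list), the SD unit and the sidedness.
- Replace d = .22 with the value at the 2:1 allocation for 300 completers: about 0.38 baseline SD on change scores, or about 0.31 if the analysis adjusts for pre-test.
- Replace 75 completers per group with numbers that follow from 2:1: 200 experimental and 100 wait-list in total, which is 100, 100, 50 and 50 if each pair is split evenly. Otherwise, state the differential completion that would yield equal groups.
- Keep the small-to-medium wording and drop the claim to detect a small effect of .22.

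This does not require a different planned test. The growth models in Data Analyses can stay, and the article fixes no four-group interaction as its test that would need replacing. The cost is a sentence or two of text and a less favourable stated sensitivity.
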